#### Participants

Overweight or obese (BMI between 25 and 40 kg/m^2^) fathers (aged 18-65 years) with a child aged between 5 and 12 years of age (i.e. primary school age) will be recruited from the local communities using the following strategies: local media releases (print, TV and radio), school newsletters items, school-based presentations, fliers distributed through community notice boards and local businesses, paid advertisements in local newspapers, local networks of sports clubs, service clubs, local government, and community health facilities. Fathers will be screened for eligibility via telephone. Ethics approval has been obtained from the University of Newcastle Human Research Ethics Committee. Written informed consent will be obtained from the fathers prior to their participation as well as child assent.

Fifty fathers will be recruited from one LGA (Maitland) and randomized to either the HDHK program or a 6-month wait-list control group. Fathers (and their children) will be stratified by BMI category (overweight [25-29.9 kg/m^2^], obese class 1 [30-34.9 kg/m^2^], obese class 2 [35-40 kg/m^2^]) and randomized using a computer-based random number-producing algorithm, to intervention or control group. To ensure concealment, the sequence will be generated by a statistician and given to the project manager. Randomization will be completed by a research assistant not involved in assessments and the allocation sequence will be concealed when enrolling participants. Fathers and their children will be assessed at baseline, post-intervention (3-months) and 6-months (3-months post-intervention).

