#### Sample size

For the RCT, based on 80% power to detect a significant weight loss difference between groups of 3 kg, assuming SD = 5 (*P *= 0.05, two-sided) a sample size of 20 fathers for each group will be needed at 6 months. Assuming a 20% attrition rate [14], a total sample of 50 fathers will be required. Participants will be blind to group allocation at baseline assessment. Once baseline assessments are completed, participants will receive a sealed envelope with a note advising their group allocation. The wait-list control group will receive no information or intervention before attending the 3- and 6-month follow-up assessment sessions. There will be a 6-month wait-list control group as (a) ethically every overweight man is deserving of an intervention and is unlikely to remain weight stable; (b) randomization to 'no' intervention for a greater length of time is unlikely to be acceptable and is likely to lead to high attrition compromising study integrity.

Stage 3 - Community effectiveness trial design

When translating evidence-based programs into real-world settings, ongoing modifications are required based on the unique characteristics of the settings and populations. Modifications will be made to the program based on both outcome and process evaluation from the community RCT and each subsequent program implementation in 2011 and these will be documented. The goal will be to develop a comprehensive model of a real-world intervention for application in communities through updating materials, developing standardized train-the-trainer education and resources and ongoing evaluation of the implementation of the intervention with a final evaluation conducted in 2012.

The HDHK program will be evaluated for effectiveness in the community roll-out using a non-randomized, prospective design. This evaluation will be conducted in both 2011 and 2012 in the five local government areas. The exclusion criteria is minimal to align with a true translational model and will only include BMI < 25 or lack of doctor's approval. Measures (detailed below) will be collected at baseline, post-intervention, and 6 and 12 months post-baseline. We aim to recruit 15-20 fathers from each area. Results from each program will be pooled and it is expected at least 200 families will participate in the community trial of the HDHK program.

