### The HDHK Intervention

The aims of the program are to help fathers achieve their weight loss goals, become healthy role models, and promote healthy behaviors for their children. Table 2 details the specific HDHK program content for each session. The 3-month HDHK program involves fathers attending seven face-to-face group sessions (90 minutes each). Four group sessions are for fathers only, and three sessions involve both the fathers and their children. These practical sessions will be conducted in local school halls and delivered by two trained facilitators.

**Table 2 T2:** HDHK sessions and program content

Session focus	Session detail
1. 'Weight loss for men' (Dads)	* Program rationale * Importance of fathers and their influence on children * Energy balance and weight loss * Nine key weight loss tips for men * Website use for eating and activity diaries

2. 'Raising active children in an inactive world' (Dads)	* Obesogenic environments * Physical activity levels, trends and benefits * Physical activity recommendations * Physical activity goals for Dads * Ideas for fitness/activity at home

3. 'Ready to rumble with Dad' (Dads & Kids)	* Rough and Tumble Play * Fun Fitness circuits * Fun and active games

4. 'Healthy eating for families - Dads matter' (Dads)	* Healthy eating benefits * Child nutrition * Food based guidelines * Role of fathers in healthy home eating environments * Authoritative feeding practices * Reading food labels

5. 'Fitness, fun and fundamental movement skills (FMS)' (Dads & Kids)	* FMS skills circuit * Rough and Tumble activities * Partner fitness challenges

6. 'Sustaining healthy lifestyles' (Dads)	* Planning meals * Australian Guide to Healthy Eating * Recommended daily intakes * Why we eat food? * Support and strategies for successful dietary changes and relapse prevention

7. 'Weight control is a journey, not a destination' (Dads & Kids)	* Program revision * Challenges and solutions * Rough and tumble activities * Ball and game skills

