#### Primary outcome measure

The primary outcome measure is body weight of the fathers at 6-month follow-up. Weight will be measured with fathers wearing light clothing, without shoes on a digital scale to 0.1 kg (model CH-150 kp, A&D Mercury Pty Ltd, Australia). Weight will be recorded twice and the average of the two measures reported. The same protocol will be followed to record children's weight.

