*Dose delivered*	To what extent were all intervention components implemented?	Facilitators HDHK research staff	* Independent self-reported checklist from Lead and Co Facilitator regarding the amount of pre-prepared content delivered and any non-delivered content (theoretical and practical) * Observation checklist of delivered content from independent observer to validate facilitator self-report checklist	* At the conclusion of each session (Checklists will be faxed to research staff post-delivery) * At least two observations per seven session program	* Calculated score based on percentage of intended content included * Percentage difference score of researcher versus facilitator average of intended content included	* Formative - informal feedback to staff prior to the next intervention session * Summative - reported after the program is complete

*Dose received*	How did participants react to the activities presented during the intervention?	Participants	* Participant evaluation of each of the attended sessions (enjoyment, amount learnt, ease of understanding content, relevance to self, likelihood of strategy use, likes and suggested changes) * Post-program evaluation (likes, dislikes, comments, attitudes before, attitudes after, program activities, facilitators, resources)	* Post-session * Post-program	* Quantitative analysis of session scores; Qualitative analysis of likes and suggestion themes per session and across the program	* Summative - reported after the program is complete

	To what extent did participants engage in recommended follow-up behavior?	Participants	* Father's log book and green slip homework activities; Kid's log book	* Father's log book (post-program); Kids log book (during and post program); Father's green slip homework (weekly)	* Level of follow-up activity completed included as a factor during quantitative analysis	* Summative - reported after the program is complete

*Reach*	What proportion of fathers attended greater than 70% of sessions (5 of 7)?	Facilitators	* Session roll for attendance	* Recorded at each session	* Level of attendance included as a mediator during quantitative analysis	* Summative - reported after the program is complete

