For the community trial, the mean change between pre and post-intervention outcomes will be analyzed using paired Student's t-test when change data are normally distributed. Wilcoxon matched pairs signed rank tests will be used for non-parametric tests. Per protocol analyses for both the RCT and the community trial will be performed for those who attended at least 70% of HDHK sessions and the follow-up assessment visits.

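### The RCT per-protocol rule requires session attendance that wait-list controls cannot have, so the supplementary attender contrast is not protected by randomisation.

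*Protocol article*

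**What the plan says.** The last paragraph of Data Analysis in the protocol article sets a single per-protocol rule for both stages: "Per protocol analyses for both the RCT and the community trial will be performed for those who attended at least 70% of HDHK sessions". The sentence goes on, so the full condition is "at least 70% of HDHK sessions and the follow-up assessment visits". No separate condition is given for RCT controls.

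Under Participants, fathers in the RCT are "randomized to either the HDHK program or a 6-month wait-list control group". The Sample size section adds: "The wait-list control group will receive no information or intervention before attending the 3- and 6-month follow-up assessment sessions". The endpoint falls at the end of that wait: "The primary outcome measure is body weight of the fathers at 6-month follow-up".

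The process evaluation table (Table 4) treats attendance as an analysis variable: "Level of attendance included as a mediator during quantitative analysis". It gives completed homework a similar role, as a factor. The table does not name the model or say which arms it covers.

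The main RCT analysis, also under Data Analysis, is a mixed model on all randomised participants with an intention-to-treat rationale.

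**The concern.** The rule works in Stage 3, where every father is offered the programme. In the two-arm RCT it asks for a behaviour that only one arm has the chance to show before the endpoint.

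Fathers who come to most sessions are probably more motivated than those who do not, and some of them would probably have lost more weight without the programme. Comparing them with unselected controls mixes that difference with the effect of attending. A reader who sees a larger per-protocol than intention-to-treat difference could take the whole excess as the benefit of a full dose, when part of it may be selection.

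**Working it through.** **1. The threshold.** The programme has seven sessions. 0.70 × 7 = 4.9, so at least 5 sessions are needed, and 5/7 = 71.4%. This agrees with the 5-of-7 figure in the Reach row of Table 4.

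**2. Controls against the threshold.** Sessions available to a control before the 6-month endpoint: 0 of 7. Required: 5 of 7. So 0 of the 20 control fathers the plan expects at 6 months can qualify on sessions. (The 20 is taken as stated; whether it is adequate is a separate matter.) Sessions attended after the wait fall after the endpoint and cannot define the set. Controls can meet the follow-up-visit half of the rule.

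**3. Two readings.**
- Both halves applied to both arms: no controls, so no between-group contrast can be estimated.
- Session half applied to the intervention arm only: attenders who returned against all controls who returned. The arms are then selected by different rules, one of them on behaviour after randomisation.

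**4. Size of the bias under the second reading.** Let p be the share of intervention fathers reaching 5 of 7 sessions. Let m1 and m0 be the mean untreated weight loss of would-be attenders and of the rest. By randomisation the control mean is p·m1 + (1−p)·m0. The attender mean minus this, with no treatment effect, is

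bias = (1 − p) × (m1 − m0).

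The document gives neither p nor the gap. Assumed: p = 0.6 to 0.8, gap = 1 to 3 kg.
- Low end: (1 − 0.8) × 1 = 0.2 kg; 0.2/3 = 7% of the 3 kg target.
- High end: (1 − 0.6) × 3 = 1.2 kg; 1.2/3 = 40%.

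**5. Cross-check with another model.** Take the plan's SD of 5 kg, a true effect of zero, and an assumed correlation ρ of 0.2 to 0.5 between propensity to attend and weight loss. With c the normal quantile at 1 − p, and φ the standard normal density,

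bias = ρ × 5 × φ(c)/p.

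- p = 0.8, ρ = 0.2: 0.35 kg (12% of 3 kg).
- p = 0.6, ρ = 0.5: 1.61 kg (54%).

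A simulation of 10,000 trials per setting, with 20 fathers per arm before selection, gave a two-sided type I error of about 5.6% and 14% at these two ends, against a nominal 5%.

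**6. The alternative has its own bias.** With no programme access in controls, the CACE is the intention-to-treat difference divided by p. This assumes that fathers below 5 sessions gain nothing. If they gain g, the result is too large by (1 − p) × g/p. For an assumed g = 1.5 kg:
- p = 0.8: 0.2 × 1.5/0.8 = 0.375 kg.
- p = 0.6: 0.4 × 1.5/0.6 = 1.0 kg.

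This is similar in size to the bias in step 4, so the threshold that defines compliance needs a sensitivity analysis.

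**The case against.** The strongest reply is that no analyst would run a two-arm per-protocol analysis without controls. The ordinary reading is attenders against controls who came back, and a full protocol or analysis plan could spell that out. This stands in part: a control group can exist in practice, and a reader who infers that the RCT has no control group at all goes further than the text. But the ordinary reading is the one that breaks comparability, and the rule is stated and extended to the RCT, not left open.

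Second, the per-protocol analysis is supplementary. That stands. Nothing in the article makes it decisive, so it does not follow that the trial's main result is compromised.

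Third, direction and size rest on assumptions. That stands too. A per-protocol estimate can exceed the intention-to-treat one because of a genuine dose effect. Requiring controls to return also selects them, which may narrow the gap. It would be wrong to say that the excess must come from selection alone.

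Fourth, on Table 4, a reader might infer that attendance and homework are inseparable from group because both are zero in controls. They are not: both vary among intervention fathers, so a model with both terms can be fitted, and the table names no two-arm model. What remains is that any link with outcome in the RCT comes from non-randomised variation within one arm.

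Fifth, the CACE is not assumption-free. Session 1 already covers weight-loss content and use of the diary website, so partial attenders may well benefit. This stands and shapes the fix.

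**Conclusion.** The concern holds for the supplementary RCT per-protocol analysis only. That wait-list controls cannot meet the session criterion before 6 months follows directly from the text. The contrast that remains in practice is non-randomised and likely, but not certain, to favour the programme. The 0.2-1.2 kg range depends wholly on the assumed 60-80% attendance and 1-3 kg gap; the second model, on different assumptions, gives about 0.35-1.6 kg. The all-randomised mixed model is untouched, and this control-group problem does not arise in the single-arm community trial. The rule should be changed, but the main inference does not depend on it.

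**What to change.** 1. **RCT:** estimate the effect of attendance as a CACE, with randomisation as the instrument and all randomised fathers kept. State the exclusion restriction. Report it for attendance at 5 or more of 7 sessions and again with compliance defined as attending any session, since the first version overstates the effect if partial attenders benefit. Give each its own confidence interval. The CACE does not by itself deal with the 20% attrition the plan allows for, so the numerator should come from the planned mixed model.
2. **If the attender contrast is still reported:** state that controls qualify by follow-up visits only, and label the result non-randomised and supplementary.
3. **Table 4 variables in the RCT:** use attendance and homework level only for descriptive dose-response within the intervention arm.

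Cost: a little extra analysis, a wider confidence interval than for the intention-to-treat difference, and an assumption that the data cannot test. No change to recruitment, visits or data collection is needed, because session rolls and homework records are already planned.

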## Discussion

The primary aim of this study is to evaluate the impact of the HDHK program in a community setting. This study will test the previously established efficacious HDHK program [14] in a larger effectiveness trial in five local government areas in the Hunter Valley in NSW, Australia. This is an area of NSW with higher than average obesity prevalence and a high population of shift workers, making this a high health risk population area [19]. Therefore, the examination of the effectiveness of a successful father-focused weight loss program within a community setting is of great importance.

Translating research results into evidence-based community programs that are widely disseminated is a major public health challenge [18]. The programs with the most potential to prevent unhealthy weight gain in children are those that are evidence-based, readily accessible, require minimal resources, and can be delivered in community settings. As a unique approach to reducing obesity prevalence in men and improving lifestyle behaviors in children, we plan to investigate the effectiveness of targeting overweight fathers to elicit changes in their own diet and physical activity habits and those of their children. Our findings will provide important information relating to the translation of HDHK which will enable it to be delivered on a larger scale and enable further studies to address long-term impact and ongoing evaluation. In addition, the HDHK community program will add to the health promotion services in regions typically having fewer allied health professionals compared to major cities.

Our community-based participatory research approach focuses on local relevance of health issues and collaborative partnerships between the researchers and community; builds on the strengths and resources of a community; and promotes capacity building. Translating efficacious interventions into community settings has the potential to make a significant public health impact. The potential public health benefits relate to our key research outcome, which is the improvement in the overall health and quality of life of participants (both fathers and children) through (a) positive changes in behaviors relating to physical activity and food intake (b) positive role modeling and engagement of fathers in their children's health and life and (c) community benefits through reductions in the burden of disease and direct/indirect health costs that are associated with poor lifestyle behaviors.
